## 11. TOXICITY AND DOSE DELAYS - MODIFICATIONS

### 11.1 Criteria for retreatment

If disease progression is not observed, patients will be retreated at the same dose level of cycle 1, unless a dose reduction is necessary as a consequence of toxicity, according to criteria listed below.

Hematological toxicity is expected to occur mainly as a consequence of treatment with vinorelbine.

In order to receive vinorelbine therapy, both on day 1 and 8 of each cycle, patients must have ANC  $\geq 1.0 \times 10^9/L$  and platelets  $\geq 75 \times 10^9/L$ .

No sorafenib interruption is mandatory in case of hematological toxicity.

In case of diarrhea, skin rash, hand-foot syndrome or hypertension, most probably attributable to sorafenib intake, the administration of vinorelbine will be allowed, at investigator's discretion.

## 11.2 Hematological toxicity

In case of neutropenia  $\geq G3$  ( $ANC < 1.0 \times 10^9/L$ ) or thrombocytopenia  $\geq G2$  (platelet count  $< 75 \times 10^9/L$ ) on day 1 of a cycle, chemotherapy will be withheld until resolution to  $ANC \geq 1.0 \times 10^9/L$  and platelets  $\geq 75 \times 10^9/L$ , with no need for dose-modification.

In the case of neutropenia  $\geq G3$  or thrombocytopenia  $\geq G2$  on day 8, the second dose of vinorelbine will be cancelled, and the treatment will be restored on day 1 of the next cycle.

If in a patient vinorelbine is postponed on day 1, or cancelled on day 8 two times as a consequence of neutropenia, the use of prophylactic G-CSF will be allowed from the following cycle. Colony-stimulating factors will be started 24-48 hours after the vinorelbine dose, and discontinued at least 24 hours prior to the next administration.

The use of stimulators of thrombopoiesis is not allowed.

If in the same patient vinorelbine infusion is postponed on day 1, or cancelled on day 8 twice as a consequence of thrombocytopenia, a dose reduction of vinorelbine is allowed (see Section 12.8).

No dose modification/reduction is mandatory for vinorelbine in case of anemia G1-2. If the anemia results in symptoms (such as fatigue) or  $G3$  ( $< 80 g/L$ ), then this can be treated appropriately, with erythropoietin and/or blood transfusions.

## 11.3 Diarrhea

The appearance of diarrhea is expected as a consequence of sorafenib administration.

In the case of diarrhea, loperamide intake, according to manufacturer's instructions, should be initiated after the third episode on the same day.

For diarrhea Grade  $\leq 2$  (increase of up to 6 stools per day over baseline), sorafenib suspension is not mandatory, but appropriate therapy with loperamide is mandatory in the presence of diarrhea Grade 2.

If Grade 2 diarrhea persists for more than 5-7 days despite loperamide, a temporary suspension of sorafenib until toxicity resolution to Grade 1 should be considered.

Sorafenib temporary suspension is mandatory in the case of diarrhea G3-4, until

resolution to Grade  $\leq 2$ .  
If diarrhea persists as G3-4 longer than 24 hours after sorafenib suspension and starting adequate therapy with loperamide or diphenoxylate/atropine, sorafenib will be eventually restarted at a lower dose level (see Section 12.8).

#### 11.4 Hand-foot skin syndrome (HFS)

As a consequence of treatment with sorafenib, patients may experience a reddening and soreness of the skin, particularly on the surfaces of the hand and feet but also in skin folds. This toxicity is referred to as hand-foot syndrome (HFS).

HFS will be graded as following:

- Grade 1: painless mild erythema, swelling, or desquamation nor interfering with daily activities;
- Grade 2: painful erythema, desquamation, or swelling interfering with, but not precluding normal physical activities; or small blisters or ulcerations less than 2 cm in diameter;
- Grade 3: blistering, ulcerations, swelling or severe pain interfering with walking or performing normal daily activities; cannot wear regular clothing;
- Grade 4: diffuse or local process causing serious infectious complications, or a bedridden state or hospitalization.

Patients will be provided recommendations to decrease its incidence and severity.

In the presence of Grade  $\geq 2$  HFS, patients must be aware of the need to hold sorafenib intake, until resolution to Grade  $\leq 1$  HFS.

A dose level decrease (see Section 12.8) will be applied for patients presenting Grade 3-4 HFS, or two separate episodes of Grade 2 HFS with an interval shorter than 3 months.

#### 11.5 Skin rash

Sorafenib treatment will continue in the presence of rash G1 and, at investigator's discretion, G2, and the use of topical products, such as emollients or low potency topical steroids, will be allowed.

In case of rash of Grade 3, patients will hold sorafenib administration, until resolution to Grade 1.

If Grade3 rash persists more than 5 days after suspension of sorafenib, or if a second Grade3 rash of any duration occurs within less than 3 months, then the treatment will be restarted at one dose reduction (see Section 12.8).

## 11.6 Hypertension

Hypertension will be graded as G1 if transient and asymptomatic, not requiring treatment. If a patient develops recurrent or persistent or symptomatic hypertension (G2), she will receive appropriate anti-hypertensive treatment, starting with a monotherapy.

Only in case of diastolic blood pressure >100 mm/Hg or symptomatic G2 hypertension, sorafenib will be suspended until diastolic blood pressure decreases to <100 mm/Hg, and symptoms resolve.

In case of G3 hypertension, requiring more than one drug, sorafenib treatment will be suspended until achievement of a good blood pressure control, and eventually resumed at a lower dose (see Section 12.8).

In case of hypertension G4 (e.g. hypertensive crisis), treatment with sorafenib will be permanently discontinued.

## 11.7 Cardiac toxicity

A Grade 3-4 cardiac event is defined as:

- a LVEF <40%, or
- a 20% decline or greater in LVEF from baseline to <50%, or
- any decrease to a value below the lower limit of normal in LVEF that is symptomatic at rest for dyspnea, orthopnea, S3 gallop, tachycardia or inspiratory crackles.

In the presence of a grade  $\geq 3$  cardiac event, sorafenib will be permanently discontinued, and the patient will be considered off-study. The responsible investigator will evaluate the utility of maintaining a vinorelbine-containing treatment.

For Grade2 asymptomatic events, with a decrease in LVEF to 40-50%, sorafenib administration will be temporary withheld. The assumption of sorafenib will be allowed if within 4 weeks from its suspension LVEF recovers above 50%. If sorafenib treatment is restored, LVEF will be assessed approximately every 28 days for the next 2 cycles, then every 2 cycles.

In case of a second LVEF drop to 40-50%, sorafenib assumption will be permanently discontinued.

## 11.8 Other non-hematological toxicities

Other toxicities will be evaluated as possibly or likely related to each study drug (also see

In the presence of adverse events that are unlikely related to the study treatment, the investigator will evaluate whether a temporary suspension of one or both drugs is necessary.

Any possibly study-related Grade  $\geq 3$  adverse event (with the exception of nausea or vomiting that has not been adequately premedicated, and vinorelbine-induced peripheral phlebitis or extravasation ulceration) will result in the suspension of the possibly responsible drug(s), until resolution to Grade 1, with a subsequent dose reduction in the following cycles.

In case of Grade 2 toxicities possibly related to study treatment, no dose suspension/reduction is mandatory, but the investigator will evaluate the need of modifying treatment schedule in case of recurrent toxicities.

## 11.9 Dose modifications

No intra-patient dose escalation for sorafenib will be allowed during the combination with vinorelbine.

Any patient experiencing at any cycle a toxicity requiring a dose reduction, will be evaluated by the investigator, who will evaluate the risks for the patient to restore therapy and the utility of continuing the study treatment at lower doses, rather than definitively terminating her participation in this trial. The investigator must be aware of the multiple therapeutic possibilities that are usually available for patients at this stage of disease.

Patients experiencing vinorelbine-induced toxicities requiring a dose reduction will be treated at a dose of 25 mg/m^2, and then 20 mg/m^2, if a second dose reduction is necessary. No further dose reductions will be allowed.

Sorafenib dose reduction is mandatory for patients experiencing a DLT (see Section 12), and recommended for patients experiencing the need of frequent drug suspensions (>twice in 2 months). Sorafenib dose can be lowered from 400 mg bid to 200 mg bid, and from 200 mg bid to 200 mg qd (up to a maximum of two dose-reductions for patients treated in cohort 2 dose level).

If a patient undergoes sorafenib dose reduction(s) during combined treatment with vinorelbine, the same dose will be maintained as monotherapy treatment, in the absence of progressive disease after completion of chemotherapy.

## 12. DEFINITION OF DOSE-LIMITING TOXICITY (DLT)

Dose-limiting toxicity is defined as one or more of the following:

- 1) Febrile neutropenia, defined as a temperature  $\geq 38.5^{\circ}\text{C}$  in the presence of ANC  $< 1.0 \times 10^9/\text{L}$ .
- 2) Grade 4 neutropenia lasting more than 5 days.
- 3) Grade 4 thrombocytopenia ( $< 25 \times 10^9/\text{L}$ ) or anemia ( $< 65 \text{ g/L}$ ).
- 4) Grade 3 thrombocytopenia ( $< 50 \times 10^9/\text{L}$ ), if lasting more than 5 days.
- 5) Grade 3 AST-ALT increase ( $> 5.0 \times \text{ULN}$ ), if lasting more than 5 days.
- 6) Grade 3 rash, if lasting more than 5 days after suspension of sorafenib.
- 7) Grade 3 diarrhea, if lasting more than 24 hours from suspension of sorafenib and adequate treatment with loperamide or diphenoxylate/atropine.
- 8) Other non-hematological toxicity of Grade  $\geq 3$ , except unpremedicated nausea or vomiting, vinorelbine-induced peripheral phlebitis or extravasation ulceration.
- 9) Impossibility to start the second cycle of therapy within 14 days from the planned day, as a consequence of toxicity.

Any patient experiencing a DLT at any cycle will be evaluated by the investigator, who will assess the utility for the patient of continuing the study treatment at lower doses, rather than definitively terminating his participation to this trial.

No patient experiencing a DLT will be retreated at the same dose. The investigator will evaluate risks and benefits for the patient, being aware of the multiple therapeutic possibilities that are usually available for patients at this stage of disease.

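### After a haematological DLT, Section 11.2 lets vinorelbine resume at the full 30 mg/m² while Section 11.9 requires only sorafenib to be reduced

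*Protocol*

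**What the plan says.** Five sections of the protocol bear on what happens to vinorelbine after severe haematological toxicity.

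- **Section 11.1** names the likely cause: "Hematological toxicity is expected to occur mainly as a consequence of treatment with vinorelbine". It lets patients be retreated at the cycle 1 dose level unless the criteria that follow call for a reduction.
- **Section 11.2** gives the count rule for dosing days. On day 1, neutropenia of Grade 3 or worse (ANC below 1.0 × 10⁹/L) or thrombocytopenia of Grade 2 or worse (platelets below 75 × 10⁹/L) delays vinorelbine until recovery, after which it resumes "with no need for dose-modification". On day 8 the dose is dropped and treatment restarts with the next cycle. After two such events due to neutropenia, "the use of prophylactic G-CSF will be allowed from the following cycle". After two due to thrombocytopenia, "a dose reduction of vinorelbine is allowed".
- **Section 11.8** covers other, non-haematological toxicities. A possibly related event of Grade 3 or higher suspends the possibly responsible drug or drugs, "with a subsequent dose reduction in the following cycles".
- **Section 11.9** says "Sorafenib dose reduction is mandatory for patients experiencing a DLT". It gives vinorelbine steps of 25 and then 20 mg/m² for vinorelbine toxicities that need a reduction, but does not link them to DLTs.
- **Section 12** lists the DLTs, including "Impossibility to start the second cycle of therapy within 14 days from the planned day, as a consequence of toxicity", and adds "No patient experiencing a DLT will be retreated at the same dose".

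**The concern.** Section 11.2 has a floor (Grade 3 neutropenia, Grade 2 thrombocytopenia) but no ceiling. It limits neither how long the toxicity may last nor how long the hold may run, and it does not set aside events that Section 12 classes as DLTs. The same patient can then fall under two rules: one that requires no change of vinorelbine dose and one that forbids the same dose without naming the drug. The only reduction that the protocol expressly requires after a DLT is of sorafenib.

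What is at stake is patient safety and consistency across centres. A patient with a serious haematological event may be re-exposed to the full dose of the drug most likely to have caused it, in a combination that Section 4 says has not yet been given to humans. Because 11.2 is permissive, one centre may reduce vinorelbine and another may not after the same event. Section 12 applies its retreatment bar to DLTs in any cycle, so the question reaches beyond the dose-escalation cohorts.

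**Working it through.** There is no sample size or error rate to recompute. The check sets the rules side by side, follows one patient through them, and works out the dose difference.

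**1. Which Section 12 events fall inside Section 11.2?**

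| Section 12 event | Covered by 11.2? |
|---|---|
| Grade 4 neutropenia for over 5 days | Yes, if present on a dosing day: 11.2 starts at Grade 3 and has no ceiling |
| Platelets below 25 × 10⁹/L | Yes, if present on a dosing day: 25 < 75 |
| Platelets below 50 × 10⁹/L for over 5 days | Yes, if present on a dosing day: 50 < 75, and 11.2 has no duration limit |
| Cycle 2 delayed by more than 14 days because of counts | Yes: 11.2 sets no longest hold |
| Febrile neutropenia (ANC below 1.0 × 10⁹/L) | Only if ANC is still below 1.0 on a dosing day |
| Grade 4 anaemia (below 65 g/L) | No: the hold-and-resume rule does not cover anaemia |

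Four of the six events overlap, three of them on condition that they are present on a dosing day. A fifth overlaps in part and the sixth does not. For febrile neutropenia that has resolved by the next dosing day, and for Grade 4 anaemia, 11.2 gives no vinorelbine dose rule at all, so there the gap is silence and not an express permission.

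**2. One patient followed through the text.** Take a patient on vinorelbine 30 mg/m² plus sorafenib 400 mg bid, with Grade 4 neutropenia for more than 5 days that is still present on day 1 of the next cycle.

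- Section 12: this is a DLT.
- Section 11.9: sorafenib must fall one level, to 200 mg bid.
- Section 11.2: vinorelbine waits until ANC is at least 1.0 × 10⁹/L (and platelets at least 75 × 10⁹/L), then may resume at 30 mg/m².
- Section 11.2, if it recurs: G-CSF is the only remedy offered for neutropenia.
- Section 11.8: does not apply, because the toxicity is haematological.

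No clause expressly requires 25 mg/m².

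**3. Size for one patient.** The inputs are 30 mg/m² on days 1 and 8 of a 21-day cycle (Section 9.1) and a first reduction to 25 mg/m² (Section 11.9).

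- Per infusion: 30 − 25 = 5 mg/m².
- Per cycle: 2 × 30 = 60 versus 2 × 25 = 50 mg/m².
- Per week: 60 / 3 = 20.0 versus 50 / 3 = 16.7 mg/m².
- Ratio: 30 / 25 = 1.20, so the unreduced dose is 20% above the reduced one. Equivalently, the reduction is 5 / 30 = 16.7%.

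**The case against.** The strongest reply is that Section 12 already settles the matter. It deals specifically with patients who have had a DLT, its bar is absolute, and it speaks of continuing study treatment at lower doses, which can be read to mean both drugs. A specific prohibition would ordinarily override a general rule for dosing-day counts, and the 11.2 wording does not forbid a reduction. That reading is possible, but it puts Section 12 in direct conflict with 11.2, with no stated order of precedence. The other reading is at least as natural: Section 9.1 escalates sorafenib only, and 11.9 ties DLTs to sorafenib only. Either way the text needs the same correction.

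A second reply is that reducing only sorafenib is a coherent design. Vinorelbine is the fixed backbone, Section 2.2 describes its neutropenia as reversible and not cumulative, and Section 4 notes a shared CYP3A pathway, so a DLT on the combination might reflect the added drug. This is a fair defence of a deliberate choice. The protocol does not state that choice, however, and Section 11.1 points to vinorelbine as the main cause.

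Some of the other side's case stands. The overlap is limited to the events in the table. The investigator must review every DLT and may reduce vinorelbine or stop treatment. The rules for MTD and recommended dose in Section 9.1, and the response analysis in Section 16.4, do not refer to the vinorelbine dose given after a DLT. Section 11.8 is a comparison only, since it was written for a different class of toxicity, and Sections 11.1 and 11.9 do not themselves contradict 11.2.

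**Conclusion.** The concern holds. As written, the protocol permits full-dose vinorelbine to resume after several haematological DLTs, although it does not require this. The only reduction it makes mandatory falls on the drug it regards as the less likely cause. This should be corrected, but it does not undermine the trial's main conclusions.

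The size is 5 mg/m² per infusion, or 60 versus 50 mg/m² per cycle, for each affected patient. That is a dose difference and not a measured harm. The number affected cannot be derived, because the protocol gives no rate of haematological DLT for this schedule; it is expected to be small. The conclusion assumes that the event is present on a dosing day or delays cycle 2, and that the first vinorelbine reduction would be the 25 mg/m² step in Section 11.9.

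**What to change.** 1. In Section 11.2, limit the no-modification rule to haematological toxicity that meets no Section 12 criterion.
2. In Section 12, state that after a haematological DLT vinorelbine resumes one level lower (25, then 20 mg/m², as in Section 11.9). State also whether the mandatory sorafenib reduction in 11.9 applies to these events.
3. In Section 11.2, redirect the cross-reference for vinorelbine reduction from Section 12.8, which does not exist in the current numbering, to Section 11.9.

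The cost is protocol wording only, with no extra patients or procedures. The one downside is lower vinorelbine dose intensity, 50 instead of 60 mg/m² per cycle (−16.7%), in the few patients who have a haematological DLT.

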## 13. CONCOMITANT MEDICATIONS

### 13.1 Anticancer treatments

No other chemotherapy, anticancer hormonal therapy, or experimental anticancer medications will be permitted during the treatment period.

Biphosphonates for known bone metastases will be allowed only if started prior to or at the same time trial therapy is initiated, but will not be allowed to be initiated during the study participation.

Patient requiring radiation therapy during the study treatment will remain on study only if the metastases do not represent progression of disease.

In these cases, patients should have study drugs withheld during the course of radiation therapy and until recovery (at least 8 days after radiation).

If there is no evidence of radiation recall reaction, such patients may be retreated with study drugs, provided that there is no sign of progression of disease.

### 13.2 Surgical procedures

In the event surgery is necessary during trial participation, both sorafenib and vinorelbine should be stopped two weeks before surgery, and resumed after complete wound healing, if there is no sign of disease progression.

### 13.3 Allowed medications

Patients will continue therapies initiated before the study start for concomitant diseases, and will receive optimal treatment for adverse events or newly diagnosed pathologies during the participation to the study. Nevertheless, any disease progression requiring other forms of anti-tumor therapy will result in discontinuation of the subject from the trial.

In particular, the following will be permitted during the trial:

- antiemetics;
- erythropoietic agents;
- skin topical products, such as emollients, low potency topical steroids or topical antibiotics;
- loperamide, or similar antidiarrhoics;
- anti-inflammatory or narcotic analgesics;
- antihypertensive medications.

All concomitant medications will be recorded with indication, dose information and dates of administration.

### 13.4 Hematopoietic growth factors

Prophylactic use of hematopoietic growth factors will be permitted for specific patients, only after documented difficulty to maintain an adequate dose-intensity of vinorelbine as a consequence of recurrent neutropenia.

If in a patient vinorelbine is postponed on day 1 three times, or cancelled on day 8 two times as a consequence of neutropenia, the use of prophylactic G-CSF will be allowed in the following cycles. Colony-stimulating factors can be started 24 hours after a vinorelbine dose, and discontinued at least 24 hours prior to the next administration.

Use of stimulators of thrombopoiesis will not be allowed.

Packed red blood cell and platelet transfusions should be administered as clinically indicated.

### 14. DISCONTINUATION OF THERAPY AND WITHDRAWAL FROM STUDY

A patient will stop receiving the study treatment and will be withdrawn from the study when any of the criteria is met:

- Progression of disease based on physical examination or radiological

- Patient's inability to tolerate therapy despite dose reduction. This includes allergic reactions not controlled with slower infusions and routine pre-medications.
  - Patient experiencing an adverse event that would mandate a dose reduction below 200 mg qd for sorafenib, or below 20 mg/m^2 for vinorelbine.
  - Withdrawal of informed consent.
  - Patient evaluated as non-compliant by the investigator.
  - Need of new anticancer treatments. Patient requiring palliative radiation therapy should have study drugs withheld during the course of radiation therapy and until recovery (at least 15 days after radiation). Such patients may be retreated with study drugs, provided that the metastases do not represent progression of disease and there is no evidence of radiation recall reaction.
  - Patient with clinical signs or laboratory test results consistent with pregnancy. The pregnancy will be followed up via the Pregnancy Monitoring Form.
- The investigator can discontinue the patient at any time, at his/her discretion.

## 15 ASSESSMENT AND REPORTING OF ADVERSE EVENTS

### 15.1 Definition of Adverse Event (AE)

An adverse event (AE) is any untoward medical occurrence in a patient or clinical investigation subject administered a pharmaceutical product/biologic (at any dose), or medical device and which does not necessarily have to have a causal relationship with this treatment.

This includes the onset of new illness and the exacerbation of pre-existing conditions, whether or not considered related to the medicinal product.

An AE can therefore be any unfavorable and unintended sign (including an abnormal laboratory finding), symptom or disease temporally associated with the use of the study treatment, as:

- occurring in the course of the use of the study drugs;
- associated with, or observed in conjunction with product abuse or overdose, whether accidental or intentional;
- associated with, or observed in conjunction with product withdrawal.

All adverse events will be recorded in the patient's medical records and on the data collection documents. The onset and end date, initial severity, change in severity grade, casual relationship to the study treatment will be recorded for each adverse event.

The severity of the adverse event and relationship to the study drug will be assessed according to specific guidelines described below.

